### Procedure

One week prior to the start of the interventions, the baseline measurement battery (secondary outcomes) will take place. Handedness will be assessed with the Edinburgh Handedness Inventory and a pre-EEG screening questionnaire will be administered. 

This includes questions about SU use of alcohol or any other substances, previous episodes of Stroke, Epilepsy, Brain Injury, or other conditions that may make wearing a cap or head garments difficult, uncomfortable, or painful. Furthermore, we will ask if participants are currently prescribed any antipsychotic, anti-depressive, or anti-anxiety medication. Quantitative and qualitative data will be collected through the outcome measuring tools (Table 1).

**Table 1 Tab1:** Representation of primary and secondary outcomes, their labels and timepoints of administration

Outcome	Measure label	Measure timepoints
Primary outcome		
Feasibility and acceptability	Participant satisfaction survey	At Week 8
	Attendance sheet	After each session
	Exit questionnaire	Following disengagement with intervention
	Focus group	At Week 9
Secondary outcomes		
Substance use (a) Days of primary substance used (b) Usage of primary substance per day Physical Wellbeing Mental Wellbeing Overall Quality of Life	Treatment Outcome Profile (TOP)	Baseline and Week 8 (end of treatment)
Retention in treatment completion rate	WDP Case management system	At week 11
Substance craving	Brief Substance Craving Scale (BSCS)	Baseline and week 8 (end of treatment)
Neural correlates of substance craving	Beta frequency band/resting state	Baseline and week 8 (end of treatment)
Levels of depressive symptoms	Patient Health Questionnaire–9 (PHQ-9)	Baseline and week 8 (end of treatment)
Neural correlates of depressive symptoms	FAA/resting state	Baseline and week 8 (end of treatment)
Levels of anxiety	Generalised Anxiety Disorder–7 (GAD–7)	Baseline and week 8 (end of treatment)
Neural correlates of anxiety symptoms	FMT/resting state	Baseline and week 8 (end of treatment)
Inhibitory control	Visual behavioral Go/No-Go task	Baseline and week 8 (end of treatment)
Neural correlates of inhibitory control	EEG event-related potential (ERP) P3	Baseline and week 8 (end of treatment)
Therapeutic alliance	The Helping Alliance Questionnaire–II	After IMT session 2 and 5
Moments of therapeutic interest	Semi-structured Interview	After IMT session 2 and 5
	Audio-visual data	During IMT session 2 and 5

Individuals allocated to GMT and IMT will be asked to attend 6 weekly therapy sessions each with a duration of 60 min. However, due to the planned EEG hyperscanning and necessary preparation time (ca. 35 min) as well as semi-structured interviews (20 min) in weeks 2 and 5 in the IMT group, participants in this group are required to attend for ca. 115 min in these weeks. Individuals allocated to CG will be asked to attend their usual care by the WDP care team. The ST that participants will receive from WDP may vary from week to week but will include a range of psychosocial and clinical interventions delivered in 1:1 and group formats. Over the 6 weeks we expect a participant to receive up to 180 min of ST (approximately 3 × 60-min WDP key work sessions—see below) but this is depending on individual needs. The participant may also attend other groups or appointments at WDP. After the interventions, GMT, IMT and CG will complete the same secondary outcomes measures again. Primary outcomes will be measured after the interventions in weeks 8 and 9 with a participant satisfaction survey and focus groups, respectively.

### Interventions

MT involves the use of sounds and music within an evolving relationship between participants and therapist to support and encourage physical, mental, social, emotional, and spiritual wellbeing. Sessions will be delivered by a qualified music therapist, registered with the UK regulator for health and care professions, the Health and Care Professions Council (HCPC). Registered music therapists must have undergone training through an accredited Music Therapy training course, which is offered in the UK either in the form of a two year full time or three year part time masters level training (accredited by the HCPC).

MT sessions will be based upon musical improvisation, composing and writing songs, analyzing lyrics of preferred songs, singing and talking. Participants are not required to have any previous instrument or other music experience. During GMT, active and passive music activities will be conducted as a group. During MT sessions participants will be introduced to a range of both electronic and acoustic instruments, including tuned and untuned percussion, from which they can choose to play and improvise freely. The music therapist will accompany participants in the improvisation. This form of improvisation, with the support of the music therapists, provides participants with an opportunity to connect with emotions and feelings connected to unconscious material. Following improvisations, the therapist and SU may identify moments of interest which can be further explored either verbally or through further improvisation. Utilizing Electronic Music Production Instruments (EMPIs) provides participants with additional creative opportunities while utilizing contemporary timbres and music making techniques, thus offering participants a way to explore their musical and cultural identities [36]. The use of EMPIs also enables the recording of the music created in the sessions, which in turn provides dual benefits: firstly, participants can, if they wish, take a copy of the music they created away, and secondly, the recording can be used in the analysis of sessions.

GMT participants will have the opportunity to share any experiences and feelings arising with the group members. Through this shared experience group members can benefit from interpersonal learning, group cohesiveness and the development of social interaction techniques. ST includes 1:1 key work sessions, other group work programs and clinical support (e.g., prescribing, counseling, and clinical interventions).

### Outcome measures

Objective (i.e., EEG-based) and subjective (i.e., multi-, and single-item questionnaires), quantitative as well as qualitative (i.e., interviews and focus groups) measures will be used to accomplish the aims and objectives of the present study (Table 1).

### Outcome measures for each participant (GMT, IMT and CG)

In this section, we describe mental health, substance use and craving measures that will be administered prior to (baseline) and after (post-intervention) the intervention; therefore, at week 1 and week 8. To measure participants’ depressive symptoms, the Patient Health Questionnaire (PHQ-9) will be completed, and a resting-state EEG frontal alpha asymmetry (FAA) will be measured. The PHQ-9 is a validated and commonly used self-report to screen for depressive symptomatology [37] and shows a good internal consistency when administered to participants with SUD (Cronbach’s α = 0.90; [38]). The FAA is a neural biomarker representing the difference between the left and right alpha activity over the frontal regions of the brain [39] and a reduced FAA has been associated with depressive symptomatology [40, 41]. To measure participants’ anxiety symptoms, the Generalized Anxiety Disorder-7 (GAD-7) questionnaire will be completed and resting-state EEG frontal midline theta (FMT) will be measured. The GAD-7 is a validated [42] and standardized [43] self-report to screen for anxiety symptomatology showing a good internal consistency when completed by SUD participants (Cronbach’s α = 0.91; [43]). FMT is a neural biomarker that has been associated with anxiety [44] and increased resting-state FMT positively correlated with the reduction of anxiety after an MT intervention for clients with depression [16]. To measure participants’ feeling of craving in the preceding 24 h, the Brief Substance Craving Scale (BSCS) questionnaire will be completed and resting-state EEG beta frequency band will be measured. The BSCS is a validated questionnaire to assess craving in the SUD population over a period of 24 h [45]. The EEG beta frequency band is a neural EEG rhythm suggested to play a role in processing abstinence-related and cue-induced craving [46]; indeed, increased resting-state beta frequency band activity in the dorsal anterior cingulate cortex and pregenual anterior cingulate cortex have been associated with craving [46]. After the resting-state EEG recordings, participants will complete a behavioral Go/No-Go task while EEG event-related potentials (ERPs) will be measured to assess inhibitory control. The visual Go/No-Go task is a straightforward behavioral paradigm requiring participants to respond with a button press when a set of stimuli are presented (circles appearing at the top right and bottom left corners of the screen) and to withhold the response when another set of stimuli, with the same probability of occurrence, is presented (circles appearing at the top left and bottom right corners of the screen) [47–49]. To measure substance use, days of primary substance used, usage of primary substance per day, physical wellbeing, mental wellbeing and overall quality of life, the Treatment Outcome Profile (TOP) questionnaire will be completed. The TOP is a psychological health scale validated in a sample of SUD participants [50] and a standard measurement tool used in community treatments services in England and Wales. Biomarkers, such as Urine Drug Screening (UDS) or breathalyzers, will not be used during this feasibility study. This is due to costs and added burdens to the participants and the hosting service. While the TOP is a self-reported measure, it is a questionnaire regularly administered to all service users and we expect it to provide indicative results of which can be followed up in further studies.

### Additional outcome measures for participants in the GMT and IMT group

In this section, we describe outcome measures that will only be administered to participants assigned to the GMT and IMT group. Each participant and the therapist will complete an attendance sheet after each GMT and IMT session to monitor participation rates. To measure and monitor for instantaneous level of craving intensity, a Craving Thermometer (in the form of Visual Analogue Scale [VAS]) will be completed before and after each GMT and IMT session by each participant [51, 52]. This measure represents a quick-scan of craving intensity and a threshold score of 3 on a craving VAS ranging from 0 to 10 has been shown to sensitively predict the presence of craving (*p* < 0.05; [51, 52]). To assess if the MT program, carried out alongside the ST, is acceptable as an intervention in a community setting, participants will complete a participant satisfaction survey at week 8. Participants will also have the chance to provide detailed feedback on the MT program through the survey. To assess the feasibility and acceptability of MT in addition to ST in a CSMTS, a focus group will be conducted at week 9 (two weeks after the end of treatment) to collect qualitative data on SU satisfaction. An exit questionnaire will be administered to participants who disengage with the intervention to gather qualitative data regarding their reasons for withdrawing.

### Additional outcome measures for participants in the IMT group

In addition to the measures listed above, and to test the feasibility of investigating mechanisms of change with neurophysiological research methods, participants receiving IMT will undertake in-session measures. The following outcome measures will only be collected at the 2^nd^ and 5^th^ sessions. To measure client-therapist alliance, the Helping Alliance Questionnaire-II (HAQ-II) will be completed by the participant and the therapist [53]. The HAQ-II is a questionnaire measuring therapeutic alliance and has been validated in a large sample of SUD [53]. To select significant-nodal moments for the client, a qualitative semi-structured interview will be conducted after the session 2 and 5. Important and emotionally relevant moments of the 2nd and 5th therapy sessions can be examined by reviewing specific time frames acquired in the AV recording of the session and the corresponding EEG concomitants [22]. Additionally, during those two sessions, EEG hyperscanning technology will be adopted to measure the brain activity from the therapist and the participant while interacting. This method has already been implemented in an MT setting by members of the research team to explore the neural correlates of client-therapist relationship during selected therapeutically interesting moments [21, 22].

### Additional outcome measures for participants in the GMT group

Following completion of the MT intervention period, each GMT participant will be interviewed (audio recorded) by the music therapist. This individual qualitative debriefing interview will focus upon participant experiences of using music technology in music therapy sessions.

### Focus groups for participants and WDP staff

Following the completion of the entire intervention, the IMT, GMT and SG will be invited to attend focus groups lasting approximately 60 min. Two focus groups will be conducted. The first one for both the IMT and GMT participants. The second focus group will only include the SG. The focus groups will capture qualitative data on SUD participants’ acceptability, session feedback and suitability. The focus group for SG will explore feasibility and future implementation.

### Electroencephalography (EEG) recording

The pre-post intervention EEG recording procedure will include a 5-min eyes-closed resting-state, after which a 5.5-min EEG ERP recording during a Go/NoGo task will be performed. Those recordings will be accomplished utilizing 32 Ag/AgCl passive electrodes (R-Net, Brain Products, GmbH, Germany). The EEG resting-state frequency bands will be analyzed with Neuroguide (NG) software [16, 54, 55] while the ERP data will be analyzed using BrainVision Analyzer software (version 2.1.2; Brain Products GmbH) and MATLAB (R2021b) [56]. The EEG hyperscanning data will be recorded throughout the second and fifth therapy session from therapist and participant utilizing 32 Ag/AgCl active electrodes (ActiCap, Brain Products GmbH, Germany). Artifact control will be guided by video recording of the IMT session and by notes taken during recording. Pre-processing and processing steps to analyze neural time-series data will be performed with BrainVision Analyzer software (version 2.1.2; Brain Products GmbH) and will follow our previously published study [22]. All baseline resting-state EEG recordings will be reviewed for potential clinically relevant findings (incidental findings) by a Consultant in Clinical Neurophysiology ([name]).

### Analysis strategy regarding the main study aim

Data analysis of the main study aim will be performed by comparing feasibility-related measures collected at the end of the treatment between participants allocated to the IMT or GMT groups. Descriptive statistics will be used to examine the rate of acceptability and satisfaction in these two experimental groups. Primary outcome measures (feasibility-related measures) that will be used are: (I) retention in treatment, which will be assessed by collecting attendance sheets and treatment status. The treatment status from participants receiving IMT, GMT and ST will be collected by WDP’s case management system 1-month post-intervention. This will provide information about retention in treatment, treatment engagement and completion rate. (II) Acceptability of treatment, which will be assessed by collecting a participant satisfaction survey as a post-intervention measure (at week 8) and implementing two post-intervention focus groups (FG1 and FG2) (at week 9). Primary outcome measures will only be administered/conducted after the end of the intervention with the aim of collecting the subjective perspective of the participants and staff involved in focus groups and will be subjected to thematic analysis using a specific thematic analysis model [57]. From this data themes will be identified pertaining (I) to participants' experience of MT in a CSMTS and (II) to participants’ experience of using music technology in music therapy.

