## Methods

### Study aims and specific objectives

The main aim of this study is to test the feasibility of implementing individual music therapy (IMT) and group music therapy (GMT) as an intervention for service users (SUs) experiencing symptoms of depression and/or anxiety and engaged with CSMTSs. In order to approach the primary aim, our objectives are (I) to measure qualitative data on SU satisfaction with the MT program, (II) to measure retention in treatment and (III) to collect their feedback over the course of the treatment. The secondary aims of this project are to examine the feasibility of applying a pre-test, posttest, and in-session assessment battery as well as to measure the effects of MT (GMT and IMT) on mental health and the neural processing associated with it. We aim to explore the effects of MT in addition to standard treatment (ST) versus standard treatment alone. Further secondary aims concern the exploration of features of the therapeutic relationship and the role of music technology in the delivery, recording, and analysis of music therapy sessions. In order to approach the secondary aims, our objectives are: (I) To measure the effects of MT in addition to ST on the following treatment outcomes in comparison to ST alone: (a) substance use, (b) physical, mental wellbeing and quality of life, (c) retention in treatment, (d) engagement with treatment, (e) completion rate, (f) emotional processing, (g) psychological symptomatology. (II) To measure reduction in craving intensity after single MT sessions. (III) To compare the effect of MT in addition to ST versus ST alone on craving, inhibitory control, depression, anxiety and the respective associated neural signatures. (IV) To explore the perceived therapeutic alliance in IMT sessions. (V) To explore the neural dynamics of emotional processing during IMT sessions. (VI) To explore SU experiences of using music technology in an MT intervention. (VII) To explore how music technology can be utilized in the subsequent analysis of audio data of musical interaction recorded during MT sessions.

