### Study design

Westminster Drug Project (WDP) is a substance misuse service provider delivering services within the UK. WDP’s Innovation & Research Unit (IRU) and the Cambridge Institute for Music Therapy Research (CIMTR), Anglia Ruskin University, have designed a mixed-methods feasibility study to address these aims and objectives. The study is designed as a three-armed study (Fig. 1) with group 1 receiving 6 weekly sessions of GMT alongside ST (see section “interventions”), group 2 receiving 6 weekly sessions of IMT alongside ST, and group 3 serving as a control group (CG), receiving 6 weeks of ST only. All participants will take part in pretest–posttest assessment (i.e., baseline and post-intervention measures) including subjective (i.e., multi-item questionnaires), behavioral (i.e., Go/No-Go task) and EEG measurements to assess several mental-health-related clinical endpoints. SUs allocated to group 2 will receive IMT while simultaneously EEG-hyperscanning is being recorded during the 2^nd^ and 5^th^ therapy sessions. After these two sessions, participants will undergo a semi-structured interview to select moments of therapeutic interest and complete a multi-item questionnaire measuring the quality of therapeutic relationship. Each participant allocated to GMT and IMT will also complete a single-item questionnaire to assess the intensity level of craving. Feedback from participants will be collected throughout the study and, where possible, requests will be implemented into the subsequent session. Engagement and treatment status of participants will be assessed 6 months post-intervention. After the intervention two different focus groups will be conducted: one involving MT participants and another involving a Staff Group (SG) of 4–8 WDP staff members who work with the service users involved. The SG focus group will explore the feasibility of MT from several perspectives, including those involved in the set-up of the MT sessions. Whilst the duration of the entire study is outlined to be a period of 3 months, participants will be committed for 8 weeks.

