### Sample size and dosage

Secondary purposes will be investigated within the frames of a feasibility study that include, as a corollary, the recruitment of a relatively small sample size to have preliminary data to determine whether interventions and research procedures are appropriate, acceptable, and practical [61].

Therefore, conclusions regarding mental health clinical endpoints as well as the therapeutic relationship and the role of music technology will be interpreted with care and presented as preliminary. Presently, positive results regarding the effectiveness of MT, as compared to a ST provided by the community, reflecting an improvement in the mental health of SUD participants have not been reported yet; for this reason, notwithstanding the small sample size limitation, it is essential to fill this gap in the literature. Additionally, analysis of the primary and secondary study aims will be performed on an intention-to-treat basis to manage drop-outs and missing data. A total of 6 IMT and GMT sessions will be offered. Patients with fewer sessions will not be excluded from data analysis (intention-to-treat principle; [62]). Nevertheless, to minimize missing data imputation, for participants not attending the post-treatment test battery at week 8, the last observation carried forward (i.e., in this case, baseline measurements at week 1) will be used.

Whilst depressive [26, 27], anxiety [26, 28, 29] and craving [30–32] symptoms have been shown to improve after MT in individuals with SUD, this will be a first attempt to study these dimensions in a community setting by measuring their neural correlates.

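### Satisfaction with music therapy is rated only at week 8, so the acceptability rate may rest on those who stayed, and the timing sentence contradicts other sections of the protocol

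*Protocol article*

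**What the plan says.** In the protocol article, 'Analysis strategy regarding the main study aim' makes acceptability the second primary outcome, "assessed by collecting a participant satisfaction survey as a post-intervention measure (at week 8") and by two focus groups at week 9. The summary measure is given as "Descriptive statistics will be used to examine the rate of acceptability and satisfaction in these two experimental groups", meaning the individual (IMT) and group (GMT) music therapy arms. On timing the section says: "Primary outcome measures will only be administered/conducted after the end of the intervention".

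Other sections describe collection before that point:

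- 'Study aims and specific objectives' lists, among the objectives serving the primary aim, "III) to collect their feedback over the course of the treatment".
- 'Study design' says: "Feedback from participants will be collected throughout the study and, where possible, requests will be implemented into the subsequent session".
- Table 1, under 'Procedure', places an attendance sheet (after each session) and an exit questionnaire ("Following disengagement with intervention") under the primary outcome of feasibility and acceptability.
- 'Additional outcome measures for participants in the GMT and IMT group' describes the content of the latter: "An exit questionnaire will be administered to participants who disengage with the intervention to gather qualitative data regarding their reasons for withdrawing".

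On missing data, 'Sample size and dosage' states that "analysis of the primary and secondary study aims will be performed on an intention-to-treat basis to manage drop-outs and missing data". For people who miss the week-8 battery, it carries the week-1 value forward.

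**The concern.** The plan has two separate weaknesses here.

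The first is a contradiction about when primary outcomes are collected. Read literally, the timing sentence excludes instruments and feedback that other sections count towards the same primary aim.

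The second concerns who contributes to the satisfaction rate. The only satisfaction survey the article describes comes at week 8. A participant who leaves after two or three sessions would have to return weeks later to give a rating. What that person is due on leaving is a form about reasons for withdrawal. If leavers are not rated, a rate computed among raters describes people who remained.

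The main conclusion of this feasibility study, and the planning of a larger trial, depend on this result. The two music therapy arms are also to be set side by side, so unequal loss between them could affect that comparison.

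**Working it through.** **Step 1: timing statements set side by side.** The timing sentence says primary measures come only after the intervention. The same section uses attendance sheets for retention, its first primary outcome, and Table 1 collects those after each session. Table 1 also lists the exit questionnaire at disengagement, which can fall before week 8. The aims and design sections add feedback during treatment. These statements cannot all hold as written.

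**Step 2: what an early leaver contributes to the satisfaction rate.**

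- Exit questionnaire: qualitative reasons for leaving; no satisfaction rating is described. Under 'Recruitment' it may be declined, and it is destroyed if the participant asks for data deletion.
- Feedback during the study: no instrument is named and Table 1 has no row for it.
- Interviews after IMT sessions 2 and 5: qualitative, and IMT only.
- Carry-forward: the week-1 value is used, but satisfaction with a therapy not yet started has no week-1 value.
- Week-8 survey: the article does not say whether leavers are approached for it.

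So no described route guarantees a rating from a leaver, and no stated rule handles its absence.

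**Step 3: possible size.** The article gives no acceptability rate, target or dropout rate, so there is no figure to reproduce. The numbers of leavers and the satisfaction levels below are assumptions. The allocation is from the abstract: 10 to music therapy, 5 per arm.

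With N allocated, d unrated and s satisfied among raters:

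- observed rate = s/(N − d)
- lower bound = s/N (no non-rater satisfied)
- upper bound = (s + d)/N (all non-raters satisfied)

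| N | d | s | Observed | Lower | Upper |
|---|---|---|---|---|---|
| 10 | 1 | 9 | 9/9 = 100% | 9/10 = 90% | 100% |
| 10 | 2 | 8 | 8/8 = 100% | 8/10 = 80% | 100% |
| 10 | 3 | 7 | 7/7 = 100% | 7/10 = 70% | 100% |
| 10 | 3 | 6 | 6/7 = 86% | 6/10 = 60% | 9/10 = 90% |
| 10 | 4 | 6 | 6/6 = 100% | 6/10 = 60% | 100% |
| 5 (one arm) | 1 | 4 | 4/4 = 100% | 4/5 = 80% | 100% |
| 5 (one arm) | 2 | 3 | 3/3 = 100% | 3/5 = 60% | 100% |

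The protocol allows for a loss like the last row: GMT continues as long as 3 participants remain.

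'Recruitment' also allows up to two early IMT dropouts to be replaced. If both go unrated and 10 others are all satisfied, 10/10 = 100% becomes 10/12 = 83% as a lower bound over everyone ever allocated to music therapy.

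**Step 4: expected bias.** If only completers are rated and counted, the bias is (proportion leaving) × (satisfaction among completers − satisfaction among leavers).

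| Assumed satisfaction, completers / leavers | 10% leave | 20% | 30% | 40% |
|---|---|---|---|---|
| 80% / 80% | 0 | 0 | 0 | 0 points |
| 80% / 40% | 4 | 8 | 12 | 16 points |
| 90% / 30% | 6 | 12 | 18 | 24 points |

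For example, 0.30 × (0.80 − 0.40) = 0.12, or 12 points. The bias disappears when leavers are as satisfied as completers.

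**The case against.** The strongest reply is that early leavers are not ignored. The exit questionnaire is itself a listed primary measure, and its free text is analysed for themes together with the satisfaction survey. IMT participants are interviewed after session 2, so someone leaving that arm just afterwards would already be due an interview. Feedback is collected throughout and acted on. This stands: a reader might infer that leavers go unheard, or that the feedback objective has no provision at all, and the article supports neither. Nor does an unnamed form in a condensed article show that mid-course feedback goes unrecorded. These sources are, however, described as qualitative, and none is said to feed the satisfaction rate.

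Second, the timing sentence continues by referring to participants' subjective views and thematic analysis, so it was probably meant for the survey and focus groups alone. That is plausible and makes the contradiction one of wording. The sentence still says primary outcome measures without qualification.

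Third, a reader might infer that the rate is biased upward. The article does not establish this. It would require leavers to be less satisfied, to be unrated at week 8 and to be left out of the denominator. Nothing bars leavers from the survey, the comparison is of participants by allocation, and those with fewer sessions are to stay in the analysis. The exact denominator may properly be left to an analysis plan. A later plan cannot, however, recover ratings that were never taken.

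Fourth, retention is reported alongside satisfaction, so heavy loss would be visible. That limits the damage but does not show how leavers would have rated the therapy.

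**Conclusion.** The concern holds in a limited form. The contradiction on timing is certain from the text and needs correcting. The gap in the satisfaction rate is real: no rating at disengagement is described, and the stated missing-data rule cannot supply one, although intention-to-treat is promised for the primary aim.

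Upward bias is a risk and not a demonstrated result. Its size depends on assumptions that the article does not give. With 3 of 10 unrated and all 7 raters satisfied, the data are compatible with anything from 70% to 100%. The lower figure is a worst case and not an estimate. With 1 to 4 unrated and all raters satisfied, the lower bound runs from 90% to 60%, and the upper bound is 100% throughout. The change is worth making because the arms are small, loss is foreseen, and the missing ratings cannot be collected afterwards.

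**What to change.** 1. Reconcile the timing sentence in the main-aim analysis section with the feedback objective, the study design section and Table 1. If the sentence was meant for the survey and focus groups only, say so.
2. Add the satisfaction survey's rating items to the exit questionnaire, so that a leaver can give a rating at disengagement.
3. Offer the week-8 survey to everyone allocated to music therapy, including those who stopped and IMT participants who were replaced.
4. For each arm, report satisfaction among raters together with the number allocated, the number of non-raters, and a lower bound that counts non-raters as not satisfied. Present this as a bound and not as the main rate: as the main rate it would replace a possible upward bias with a built-in downward one.

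The cost is a few extra items on an existing form, an attempt to contact leavers at week 8 and two more columns in a table. The reported figure may be less favourable. Participants remain free to decline or to have their data deleted, so some non-raters will remain, which is why their number should be shown.
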